#### Sample size considerations

Our sample size estimation is based upon the desire to detect a 15% difference between the WWCM interventions and controls in the proportion of 5% weight responders with an alpha level of 0.05 and a power of 0.90. We assume that the enhanced control arm will result in a 5% weight loss in 20% of subjects (i.e., the control event rate = 20% at one year) [38]. Given these parameters, the minimal required sample size will be ~180 patients per arm or 540 patients total (http://statpages.org/proppowr.html). As losses to follow-up have reached 30% in previous obesity related trials; [39] we will also adjust for a 30% potential drop out rate. Therefore, our final estimated sample size will be 220 patients per arm, for a total sample size of 660 patients.

We chose a 5% weight loss threshold as the primary outcome measure of individual patient success (rather than using mean absolute body weight or a similar continuous parameter) based upon the recommendations of current consensus guidelines, which endorse this degree of weight loss as the minimum target to achieve clinically meaningful health benefits after 6–12 months of intervention [10]. We chose a 15% absolute difference between study arms as the minimum clinically worthwhile (important) difference (MCID) by consensus of clinical experts and trials methodologists and have used this type of consensus-based threshold definition in prior studies [40]. We felt that if the WWCM program produced less than a 15% improvement in weight loss [5% response] compared with controls it would not be worth continued funding - unless very compelling benefits on humanistic outcomes or cost-effectiveness were also demonstrated. We partly based our rationale for choosing this threshold on the opinions of prior consensus-based expert panels, that have proposed a 10% MCID for 1-year weight change patients with type 2 diabetes (while recognizing that weight reductions in type 2 diabetics are generally lower than non-diabetics) and a 15% MCID for statin uptake in patients with coronary disease [41,42].

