### Statistical analyses and sample size considerations

The primary outcome comparisons of interest are between the in-person WWCM intervention and controls and the online WWCM intervention and controls. Subsequent analyses will compare outcomes between the in-person and online interventions. No adjustment for multiple testing will be performed [36].

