#### Data analysis

First, variables will be examined descriptively and graphically, including assessments of temporal trends and tests of normality. Second, the 3-month and 9-month mean change from baseline measures in each outcome will be calculated and compared between cases and controls using unpaired t-tests for continuous outcomes and chi-squared tests for dichotomous ones. Third, multivariable predictors of the 9-month change in a given outcome will be identified using appropriately constructed and calibrated linear regression models for continuous outcomes or logistic regression models for dichotomous ones. Herein, we present a detailed example of our modelling strategies for body weight. First, the proportion of patients achieving 5% weight loss (5% responders, a value widely considered as a clinically worthwhile weight change) [10] and the mean 9-month change in weight will be calculated in each study arm. Second, chi-square tests will examine for significant differences between cases and controls in 5% response rates and unpaired t-tests will examine for significant differences in mean body weight change scores. Third, a multivariable logistic regression model for 5% responders and a linear regression model for mean body weight will be constructed to examine the independent effect of the WWCM program on the 9-month change in 5% response rate or mean body weight, adjusting for any statistically significant (P<0.1) or clinically important between group differences. Missing data for weight change will be addressed using a conservative ‘baseline-value carried forward’ approach and examined in a sensitivity analysis using group mean-imputation methods to confirm the robustness of results [37]. All analyses will be conducted according to the “intention to treat principle”. No interim analyses, for either efficacy or futility purposes, have been planned.

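### The step from about 180 to 220 patients per arm does not make the 30% dropout adjustment that the protocol claims, and the power at 30% loss depends on what the 20% and 35% response rates mean

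*Protocol article*

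**What the plan says.** All the inputs are in the Protocol article, under Clinical endpoints, Sample size considerations. The primary outcome is binary: "We chose a 5% weight loss threshold as the primary outcome measure of individual patient success". The design targets an absolute difference of 15 percentage points between a WWCM arm and control, "with an alpha level of 0.05 and a power of 0.90". The control response is put at 20% ("the control event rate = 20% at one year"), so the intervention rate is 35%. From this the protocol concludes that "the minimal required sample size will be ~180 patients per arm or 540 patients total". It notes that losses in earlier obesity trials have been as high as 30%, and continues: "we will also adjust for a 30% potential drop out rate. Therefore, our final estimated sample size will be 220 patients per arm", 660 in total. The Abstract (Methods/Design) and the Study design section repeat 220 and 660.

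Two other statements bear on the point. Under Statistical analyses and sample size considerations: "No adjustment for multiple testing will be performed", so alpha is 0.05 for each comparison. Under Clinical endpoints, Data analysis, the analysis is by intention to treat, and "Missing data for weight change will be addressed using a conservative" method that carries the baseline value forward.

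**The concern.** Three printed figures do not fit together: a minimum of about 180, a 30% allowance, and a final 220. Taking 30% away from 220 leaves 154, which is 26 below the protocol's own minimum.

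The missing-data rule adds a second difficulty. A patient whose baseline weight is carried forward shows no weight change and is therefore a non-responder. Dropout then does not reduce the number analysed; it may instead lower the response rates. Whether it lowers them below 20% and 35% depends on how those rates were defined, and the protocol does not define them.

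At stake is the stated power of the primary comparison. The same section says that a gain below 15 percentage points would not justify continued funding unless there were compelling humanistic or cost-effectiveness benefits. Someone weighing a non-significant result should know whether the risk of missing a true 15-point difference was planned at 10% or is nearer 16 to 20% at the dropout rate the protocol chose.

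**Working it through.** **Inputs** (Protocol article, Clinical endpoints, Sample size considerations): p1 = 0.20, p2 = 0.35, difference 0.15, alpha 0.05, power 0.90, dropout 30%, base n about 180, final n 220. Sidedness is not stated there. I assume two-sided, because a one-sided test needs only 150 per arm and does not reproduce 180.

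**1. Reproduce the base figure.**

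- Unpooled: n = (1.960 + 1.282)² × (0.20×0.80 + 0.35×0.65) / 0.15² = 181 per arm.
- Pooled under the null (mean rate 0.275): n = 185.
- Arcsine: n = 183.
- With continuity correction: n = 198.

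The first three agree with about 180, so the base figure is sound.

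**2. Apply the 30% allowance.**

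- Standard: 180 / (1 − 0.30) = 257.1, so 258 per arm, 774 in total.
- Shortcut: 180 × 1.3 = 234 per arm.
- Starting from 185 instead, the two figures are 265 and 241, further from 220.

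Neither method gives 220. Going from 180 to 220 is a 22% mark-up (220/180 = 1.222), which in completer numbers covers 1 − 180/220 = 18.2% loss.

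**3. Power among completers at 30% loss.** 220 × 0.70 = 154 per arm. Power = Φ{[|p1 − p2| − 1.960 √(2p̄(1 − p̄)/n)] / √([p1(1 − p1) + p2(1 − p2)]/n)}. With n = 154: Φ{(0.150 − 0.0997)/0.0502} = Φ(1.002) = 84.2%. With continuity correction it is 80.9%.

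**4. Power under the planned analysis (all 220 analysed, baseline carried forward).**

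- *Reading A: 20% and 35% are completer rates, with 30% dropout in each arm unrelated to response.* The rates become 0.20 × 0.70 = 14% and 0.35 × 0.70 = 24.5%. With n = 220: Φ{(0.105 − 0.0737)/0.0373} = Φ(0.841) = 80.0%. For 90% power, 295 per arm would be needed.
- *Reading B: 20% and 35% already count dropouts as non-responders.* The rates stay at 20% and 35% with n = 220: Φ{(0.150 − 0.0834)/0.0420} = Φ(1.586) = 94.4%. No inflation is needed.

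**5. Power of 220 per arm by dropout rate** (baseline-carried-forward column is Reading A).

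| Dropout | Completers only | Baseline carried forward |
|---|---|---|
| 10% | 92.0% | 90.9% |
| 15% | 90.4% | 88.8% |
| 18% | 89.3% | 87.3% |
| 20% | 88.7% | 86.2% |
| 25% | 86.6% | 83.3% |
| 30% | 84.2% | 80.0% |

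Under Reading A with baseline carried forward, power stays at 90% up to about 12% loss (90.1% at 12%).

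**The case against.** The best defence is that the planned analysis loses nobody. All 220 per arm are analysed, so 154 is a completer count, and 84% describes a completers analysis that the protocol does not name. If 20% and 35% were meant as rates with dropouts counted as non-responders, power is 94.4%. This stands as far as it goes: the 80% figure is conditional on Reading A, on equal dropout across arms, and on dropout unrelated to response. It does not rescue the sentence about dropout. On Reading B no adjustment was called for, yet the protocol says it made one of 30%, and 220 is not the result of one.

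A second defence is that 30% is an upper figure. The protocol calls it a potential rate, and its humanistic sample-size example uses 10% attrition. At 10% loss, 220 per arm gives 92.0% among completers and 90.9% under Reading A. That also stands, and it limits the point. A reader might infer that the trial lacks 90% power whatever happens. The document does not support that: the shortfall arises at or near the 30% the protocol says it has covered, and not at low dropout.

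Third, power of about 80% is a conventional level, and the funding statement refers to a 15-point threshold with stated exceptions rather than to significance alone. This is fair. It lowers the severity but leaves the arithmetic wrong.

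The article's condensed form is no defence, because base figure, allowance and result are all printed and disagree.

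**Conclusion.** Wrong as written; moderate severity. The figure of about 180 per arm reproduces. The claim that 220 adjusts it for 30% dropout does not: the adjusted figure is 258, or 234 by the shortcut. This conclusion rests only on the protocol's own numbers.

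The cost in power is less certain. At 30% loss it is about 84% among completers. Under the planned baseline-carried-forward analysis it is about 80% on Reading A and about 94% on Reading B, and the protocol does not choose between them. The type II error at 30% loss is therefore about 16% or 20% on the completer-rate reading, against the stated 10%. All these figures assume a two-sided test without continuity correction.

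It would go too far to say that only 154 patients per arm are evaluable, or that 80% is the power of the primary analysis. The first ignores the intention-to-treat rule; the second depends on assumptions that the protocol does not state. Estimand, analysis method and type I error are not affected.

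**What to change.** Keep 220 per arm and change the wording of the Sample size considerations section:

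1. Remove the claim that 220 per arm adjusts for 30% dropout.
2. State whether 20% and 35% are completer rates or rates that count dropouts as non-responders.
3. Restate power at 30% loss on that basis. For completer rates: about 84% among completers and about 80% under baseline carried forward, the latter assuming equal dropout across arms that is unrelated to response. For rates that already count dropouts as non-responders: about 94%, with no inflation needed.

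Do not simply substitute a statement that 220 allows for 18% loss. That holds for completer numbers only; under baseline carried forward with completer rates, 18% loss gives about 87% power, and 90% holds only to about 12% loss.

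The cost is wording. No patients are added and no analysis changes. On the completer-rate reading, the stated power becomes less favourable.

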### Humanistic endpoints

#### Outcomes

The instruments to be used to assess health related quality of life (SF-12, EQ-5D and PHQ-8), self-efficacy (WEL), depression (PHQ-8) and patient satisfaction (PSQ) are described above. The mental and physical domains of each instrument (where applicable) will be examined in subgroup analyses and (where available) compared with population-based normative data available for the Alberta population.

#### Data analysis

Descriptive analyses will be performed and data will be examined graphically and serial changes described. Because these are self-reported data collected every 3 months, we will use a “last-value carried forward” approach to handle missing data as our primary analytic strategy. For example, temporal trends in the SF-12 will be assessed graphically and using analysis of variance (ANOVA) as a test of trends over time. Multivariable, adjusted 9-month changes in continuous measures will be assessed using linear regression in a manner similar to that detailed for the clinical outcome analysis. Patient satisfaction will be categorized as a dichotomous variable [31] and multivariable predictors of deterioration in satisfaction will be determined in serially constructed models.

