### Health consequences of protracted waits for bariatric specialty care

The health consequences of protracted waits for bariatric care have not been well studied. To our knowledge, only cross-sectional analyses have been published to-date. The findings suggest that self-reported health is markedly impaired in subjects wait-listed for bariatric care.

In 150 severely obese patients wait-listed for entry into Edmonton Weight Wise who had been waiting for 64±76 days (i.e., only recently added to the wait list), the mean health status, measured using a visual analogue score, (VAS) score was 49 out of 100. This is markedly lower than mean VAS scores for community-dwelling Albertans (85), patients with diabetes (66) and patients with chronic obstructive pulmonary disease (65) [27]. Two thirds (62%) of patients agreed or strongly agreed that waiting was contributing to physical, mental and financial deterioration and 86% also reported worsening of physical symptoms over time [27].

A Norwegian study in 128 severely obese patients reported that mental and physical Short Form-12 (SF-12) component scores were markedly lower than population norms [28]. Another study concluded that the HRQL of 75 wait-listed Finnish patients measured using the generic 15D instrument was ‘significantly worse-off’ compared to the general population [29].

In aggregate, these findings indicate a substantial and heretofore largely unrecognized and under-appreciated degree of health impairment in patients wait-listed for bariatric care. Importantly, patients report that protracted waits are directly contributing to deteriorations in quality of life and health. Confirmation of these findings using controlled, observational study designs is required.

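### Last-value carried forward is the primary method for missing humanistic scores; it can bias the 9-month arm contrast, and no sensitivity analysis specific to these scores is named

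*Protocol article*

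**What the plan says.** Under Humanistic endpoints, Data analysis, the protocol article adopts last-value carried forward as the "approach to handle missing data as our primary analytic strategy". The reason is one clause: "Because these are self-reported data collected every 3 months". The section then names two analyses:

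- For trends, with the SF-12 as the example, it plans graphs and "analysis of variance (ANOVA) as a test of trends over time". It does not say whether this is a repeated-measures form.
- For the effect at month 9, "Multivariable, adjusted 9-month changes in continuous measures will be assessed using linear regression", "in a manner similar to that detailed for the clinical outcome analysis".

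For weight change (Clinical endpoints, Data analysis), missing values are set to baseline, and the result is to be "examined in a sensitivity analysis using group mean-imputation methods to confirm the robustness of results". That sentence concerns weight change. The humanistic section names no counterpart. Its cross-reference to the clinical analysis is attached to the regression and leaves open whether the missing-data check is included.

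**The concern.** LOCF freezes a patient's score at the last visit attended and enters it as if it had been measured at month 9. This does no harm to the arm contrast only when scores do not move, or when dropout and trajectories are alike across arms. The protocol gives reasons to doubt each condition.

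- **Scores are expected to move.** The Background reports patients' statements that "protracted waits are directly contributing to deteriorations in quality of life and health". Under Procedures, everyone enters multidisciplinary care at month 3. The humanistic sample size example assumes a 10-point change. A patient lost before month 3 carries a baseline score to month 9, and one lost before month 6 carries a pre-clinic score.
- **Attrition may differ by arm.** Objective 1 includes decreasing Adult Clinic attrition compared with controls, and attrition is to be compared between arms. Leaving the clinic is not the same as a missing questionnaire, but the two are plausibly linked.
- **Dropout may be large.** The primary sample size allows for 30%; the humanistic example uses 10%.

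Collection every 3 months is no reason for LOCF. It is the setting in which a repeated-measures model can use every observed score.

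These outcomes are secondary but can be decisive. Under Clinical endpoints, Sample size considerations, a program that falls short of the 15% threshold could still merit funding if humanistic or cost-effectiveness benefits were very compelling.

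**Working it through.** The protocol gives no figure for the effect of LOCF, so there is none to reproduce. The check asks how large a false difference LOCF creates when both arms truly change by the same amount.

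**Inputs from the protocol article.** Visits at 0, 3, 6 and 9 months; 220 per arm; SD 19 and a 10-point change (humanistic sample size example); dropout of 10% (same example) and 30% (primary sample size).

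**Assumptions.** Linear change *D* over 9 months. A fraction *a* drops out, one third each before months 3, 6 and 9, independently of the scores. SD 19 at every visit. Within-patient correlation ρ of 0.5 to 0.7. The 6-point change and the unequal dropout splits are illustrations.

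**Step 1: mean change under LOCF.** Dropouts contribute 0, *D*/3 or 2*D*/3, on average *D*/3. So

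E(change) = (1 − a)·D + a·D/3 = D·(1 − 2a/3).

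- D = 10, a = 0.10: 10 × 0.933 = 9.3.
- D = 10, a = 0.30: 10 × 0.80 = 8.0.

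If only one arm changes by 10 points and dropout is 30% in both, the true difference of 10 appears as 8.0.

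**Step 2: false difference when both arms change by D.** It equals D × (2/3) × (difference in dropout).

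- D = 6, 30% vs 15%: 6 × 0.80 = 4.8 against 6 × 0.90 = 5.4, a difference of 0.6.
- D = 10, 30% vs 15%: 10 × (2/3) × 0.15 = 1.0.
- D = 10, 40% vs 20% or 30% vs 10%: 10 × (2/3) × 0.20 = 1.3.
- Equal dropout: 0.

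The sign follows the direction of change. If the program retains more patients, LOCF favours it when scores improve and penalises it when scores fall, so it is not reliably conservative.

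**Step 3: effect on type I error.** SD of change = 19 × √(2(1 − ρ)), which is 19.0 at ρ = 0.5 and 14.7 at ρ = 0.7. SE of the arm difference = SD × √(2/220), which is 1.81 and 1.40. With z = bias/SE, the rejection rate is P(Z > 1.96 − z) + P(Z < −1.96 − z).

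| Change, dropout | Bias | z (ρ 0.5 / 0.7) | Type I error, formula | Simulated |
|---|---|---|---|---|
| 6 points, 30% vs 15% | 0.6 | 0.33 / 0.43 | 6.3% / 7.1% | 6.4% / 7.5% |
| 10 points, 30% vs 15% | 1.0 | 0.55 / 0.71 | 8.6% / 11.0% | 8.5% / 10.8% |
| 10 points, 40% vs 20% | 1.3 | 0.74 / 0.95 | 11.4% / 15.8% | 12.0% / 16.5% |
| 10 points, 30% vs 30% | 0 | 0 / 0 | 5.0% / 5.0% | 5.1% / 4.9% |

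Simulation: 20,000 runs, t-test on LOCF change scores.

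**Step 4: carried values counted as observed.** Take D = 10, a = 0.30, ρ = 0.5. One tenth of patients have a change of exactly zero, so the noise variance is 0.9 × 361 = 324.9. The spread of group means adds (0.7 × 100 + 0.1 × 0 + 0.1 × 11.1 + 0.1 × 44.4) − 64 = 11.6. The SD is √336.5 = 18.3 and the SE is 1.75, against 1.81 with no missing data. Losing 30% of patients thus looks like a small gain in precision.

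**The case against.** **The bias is conditional and modest.** This stands. With equal dropout and equal trajectories there is no between-arm bias. A 0.6-point difference is about one third of a standard error (0.6/1.81) and about 0.03 SD. The higher error rates need a 10-point common change and a 20-percentage-point dropout imbalance, which the protocol does not predict. The Background evidence of deterioration is cross-sectional patient report, which the article itself says needs confirmation.

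**The ANOVA.** A reader might infer that the trend test treats four scores from one patient as independent, and that the error bars of the arm contrast are therefore wrong. The document does not support this. It says "analysis of variance (ANOVA) as a test of trends over time", which does not exclude a repeated-measures form, and a condensed article may leave that detail to the full plan. The treatment effect comes from regression on one 9-month change per patient, so ignored within-patient correlation cannot distort its standard error. Inflated type I error from pooling visits to compare arms would belong to an analysis that the protocol never states.

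**The QALYs.** A reader might infer that LOCF-filled EQ-5D scores enter the economic model. The economic section does not say how missing utilities are handled, and it does plan sensitivity analyses on EQ-5D differences. The link is possible but not stated.

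**A standard mixed model may lose patients.** With baseline as a covariate and only post-baseline scores as outcomes, patients lost before month 3 drop out of the analysis, which sits badly with the intention-to-treat statement. This stands and shapes the fix.

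**Conclusion.** The concern holds for LOCF. It is fixed as the primary method for the humanistic scores, its stated reason does not support it, and no sensitivity analysis specific to these scores is named. It can bias the 9-month arm contrast in either direction when dropout or trajectories differ by arm, and it counts carried values as data.

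Under the stated assumptions the false difference runs from 0 to 1.3 points, and type I error from 5% to about 16%. The linear course, the even dropout, the imbalance and the correlation are assumptions, so these figures show a range and do not forecast the trial. The 5% responder outcome is unaffected. The change should be made because humanistic benefit may carry a funding decision and a better method needs only data already planned.

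**What to change.** Make the primary humanistic analysis a likelihood-based repeated-measures model on the scores at 0, 3, 6 and 9 months, with arm, visit, arm-by-visit and centre. Keep baseline as one of the outcomes, with its mean constrained to be equal across arms, so that patients lost before month 3 stay in. Read the month-9 contrasts from this model. Multiple imputation is an acceptable alternative.

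For dichotomous satisfaction, use multiple imputation or a mixed logistic model. Retain LOCF as a named sensitivity analysis. The model's visit terms can replace the ANOVA trend test, which also settles its form.

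The cost is analysis wording and slightly more programming, with no new data. The result then rests on a missing-at-random assumption, which should be stated.

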## Objectives

The EVOLUTION Trial is designed to:

1. Assess the clinical effectiveness of the WWCM program in reducing weight, improving obesity-related comorbidity and decreasing Adult Clinic attrition rates compared to controls.

2. Determine if the WWCM program improves humanistic outcomes including health-related quality of life, patient satisfaction, self-efficacy and readiness-to-change compared to controls.

3. Determine the incremental cost and cost-effectiveness of the WWCM program.

4. Compare the in-person delivery of WWCM content to online delivery in terms of efficacy and cost-effectiveness.

In aggregate, these objectives will assess the program’s impact on a comprehensive range of outcomes important to patients, providers, and policy-makers. Because the WWCM program is intended to prime patients for success as they receive care in the Adult Clinic, the primary outcomes will be measured prior to attending WWCM modules and then repeated six months after entry into the Adult Clinic.

We hypothesize that both online and in-person delivery of the WWCM intervention will reduce body weight and improve clinical and humanistic outcomes at 9 months compared to the control group. Furthermore, we hypothesize that the in-person version of the intervention will be more effective (as a consequence of greater interpersonal contact) but also more costly than the on-line version. Although we hypothesize that the program will be beneficial, this is by no means certain. It is possible that outcomes in the groups receiving the WWCM intervention will be no better than controls, only marginally better, or improved but not in a cost-effective manner. This underscores the need for rigorous program evaluation to ensure that current program delivery - as well as potential future expansion - is warranted.

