**Figure 1 F1:**
[figure not shown]
Study overview.

1. **Sociodemographic data (baseline only):** This includes age, sex, race, marital status, household income and employment status.

2. **Obesity-related comorbidities and past medical history:** includes blood pressure taken with a Watch BP® automated monitor (three readings simultaneously in each arm; first reading discarded and the latter two averaged; higher arm average used as the primary endpoint), fasting lipids and glucose, A1c, creatinine, alanine aminotransferase (ALT) smoking status and cardiovascular medications.

3. **Specific obesity-related variables:** weight, height (using a clinic based stadiometer), BMI.

4. **Quality of life and utility measurement:** Validated generic health related quality of life (SF-12 [35] and EQ-5D [30]) instruments will be used. Preference-based utilities will be measured using the EQ-5D.

5. **Satisfaction with medical care:** assessed using two questions from the Patient Satisfaction Questionnaire (PSQ) [31] that will be scored on a 5-point Likert Scale.

6. **Self-efficacy:** Obesity-specific self-efficacy will be measured using the validated Weight Efficacy Life-Style Questionnaire (WEL), a 20-item instrument that assesses self-efficacy across 5 situational factors (negative emotions, availability, social pressure, physical discomfort and positive activities) [32].

7. **Screening for Depression:** the Patient Health Questionnaire (PHQ-8), a validated screening tool for depression, will be used [33].

8. **Readiness-to-Change:** assessed using a a Visual Analogue scale ranging from 0 to 10.

9. **Attrition Rates (at 6 and 9 months only):** attrition rates within the multidisciplinary clinic will be assessed and compared between study arms.

10. **Costing Data:** Costing will adhere to the three-step micro-costing technique of identification, measurement, and valuation of resources. We will determine the overall and per-patient total and incremental costs of the two versions of the WWCM program and the control arm [34,35]. Start-up costs and on-going program delivery costs for each study arm will be tabulated. The cost per patient will be estimated using the current enrolment in the WWCM, as well as best- and worst-case scenarios (minimal and maximum session capacity) [34,35].

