#### Sample size considerations

The sample size of 660 subjects has more than adequate power. For example, for a nine month change in SF-36 domains such as physical function, with baseline score of 60, SD 19 [43], a deterioration of 10 points, two-sided alpha=0.05, beta=0.90, and a 10% attrition rate, only 85 total patients would be required. Similarly, for an outcome such as satisfaction, with baseline measures of 70% satisfied with care, a 30% deterioration in satisfaction over 1 year, and otherwise similar power-related assumptions, 136 total patients are required.

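### Patient satisfaction is collected on a 5-point scale but analysed as a dichotomy; an ordinal model would usually be more sensitive at almost no cost

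*Protocol article*

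**What the plan says.** Data collection and outcome measures, item 5, has satisfaction with medical care "assessed using two questions from the Patient Satisfaction Questionnaire (PSQ) [31] that will be scored on a 5-point Likert Scale". Objective 2 asks whether the program improves humanistic outcomes, including "patient satisfaction, self-efficacy and readiness-to-change compared to controls".

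Under Humanistic endpoints, Data analysis, the scale of analysis is set: "Patient satisfaction will be categorized as a dichotomous variable [31". The same sentence adds that "multivariable predictors of deterioration in satisfaction will be determined in serially constructed models". Continuous humanistic measures are to be analysed by linear regression. Missing self-reported values are carried forward from the last observation.

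Under Humanistic endpoints, Sample size considerations, the satisfaction example starts "with baseline measures of 70% satisfied with care, a 30% deterioration in satisfaction over 1 year" and arrives at 136 patients in total. It takes over the settings of the preceding example, "two-sided alpha=0.05, beta=0.90, and a 10% attrition rate".

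**The concern.** A response recorded in five ordered categories is reduced to two before analysis. If the cut separates categories 1 to 3 from 4 and 5, a patient who moves from 4 to 5, or from 1 to 2, counts as unchanged. With 70% satisfied at the start, only the other 30%, about 66 of 220 per arm, could register an improvement.

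The article argues for its other main dichotomy, the 5% weight-loss responder, from consensus guidelines and explains why it was preferred to a continuous measure. It offers no comparable argument for satisfaction.

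The stake is modest but real. The sample size section for the clinical endpoints allows strong humanistic benefit to justify continued funding of a program that misses the 15-point weight target. An insensitive scale makes a satisfaction benefit harder to detect with data the trial will already hold.

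**Working it through.** **Inputs from the protocol article.** 70% satisfied at baseline; 30% deterioration; two-sided alpha 0.05; beta of 0.90 read as power 0.90; 10% attrition in the humanistic example; 220 randomised per arm; 30% dropout allowed for trial-wide, which leaves 220 × 0.70 = 154 per arm.

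**Inputs assumed because the article gives none.** A 10-point difference between arms, a cut between categories 3 and 4, the distribution over the five categories, and the form of the shift.

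**1. The article's own figure.** Take the 30% as absolute (70% to 40%), with mean proportion 0.55:

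n = [1.96·√(2·0.55·0.45) + 1.282·√(0.21 + 0.24)]² / 0.30² = (1.379 + 0.860)² / 0.09 ≈ 55.7, so 56 per arm.

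The continuity correction raises this to 62.2, so 63 per arm and 126 in total. Allowing for attrition, 126/0.90 = 140, close to the stated 136. Read as relative (70% to 49%), the uncorrected formula gives 113 per arm, 226 in total, or 252 with attrition rounded up per arm. That does not match.

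**2. Power of the dichotomy at the article's effect, 154 per arm.** Power = Φ{[d − 1.96·√(2p̄(1−p̄)/n)] / √[(p₁(1−p₁) + p₂(1−p₂))/n]}.

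- 70% v 40%: above 99.9%.
- 70% v 49%: (0.210 − 1.96 × 0.0559)/0.0546 ≈ 1.84, so 96.7%.

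At most about 3 points could be lost here.

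**3. Power of the dichotomy for an assumed 10-point difference.** For 70% v 80% at 220 per arm, (0.10 − 1.96 × 0.0413)/0.0410 ≈ 0.465, so 67.9%. The other cases are in the table.

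**4. Power of the ordinal comparison under proportional odds.** For 70% v 80% the common odds ratio is (0.80/0.20)/(0.70/0.30) = 1.714, with logarithm 0.539. Whitehead's formula gives information V = N(1 − Σp̄ₖ³)/12 and power Φ(|log OR|·√V − 1.96). For a control distribution of 10/10/10/35/35 and N = 440, Σp̄ₖ³ = 0.111. Then V = 32.6, and Φ(0.539 × 5.71 − 1.96) = Φ(1.12) = 86.8%. The tie-corrected rank test gives 86.6%, and the table uses that test.

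| Analysis; control distribution, categories 1–5 (%) | 70 v 80, 220/arm | 70 v 80, 154/arm | 70 v 60, 220/arm | 70 v 60, 154/arm |
|---|---|---|---|---|
| Dichotomy | 67.9 | 52.7 | 59.5 | 45.2 |
| Ordinal; 10/10/10/35/35 | 86.6 | 72.6 | 72.7 | 57.2 |
| Ordinal; 2/8/20/50/20 | 85.1 | 70.7 | 70.0 | 54.6 |
| Ordinal; 3/7/20/60/10 | 80.3 | 65.1 | 66.5 | 51.4 |
| Ordinal; 1/2/27/68/2 | 71.4 | 55.9 | 61.5 | 46.9 |

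Over seven spread-out distributions (three shown), the gain for 70% v 80% is 12 to 19 points at 220 per arm and 12 to 20 at 154. For 70% v 60% it is 7 to 13 and 6 to 12. In the last row, where 95% of answers fall in two categories, the gain is only about 2 to 3.5 points.

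**5. Other forms of shift.** A shift on a latent normal scale at 220 per arm gives gains of 13 to 18 points, or 6 to 8 in the concentrated case, so the gain does not hang on proportional odds alone. If instead the 10 points move only from category 3 to category 4, the ordinal test loses 7 to 58 points against the dichotomy at 220 per arm.

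**The case against.** The strongest reply is that nothing here is misstated or contradictory. The dichotomy is prespecified, concerns a non-primary outcome, and carries a citation. The effect the article plans for is so large that the dichotomy already has at least 96.7% power at 154 per arm. A loss appears only at an effect a third that size (10 points against 30), which the article never targets. All of this stands, and it limits the weight of the point. It does not show the cut to be harmless for Objective 2, because the planning example describes deterioration over a year and the article states no between-arm difference in satisfaction.

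Two stronger readings are tempting. A reader might infer that the cut costs a fixed 10 to 19 points of power. The document does not support that: it gives no 10-point target, no distribution over the categories and no form of shift, and the result moves from about 2 to 20 points or turns negative as these change. A reader might also infer that the cut is unjustified. The citation is attached to the dichotomisation itself and its content is not available here, so one can say only that the article states no rationale of its own.

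The cut-point is inferred as well. The data analysis section names none, and a split at satisfied versus not is read back from the power example. A condensed article may leave such scoring detail to the full protocol. Choosing a two-category analysis is different, because the article states that choice outright.

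Finally, carrying the last value forward keeps patients in the analysis, so 220 per arm is nearer the planned analysis than 154. The gain is similar at both sizes.

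**Conclusion.** The point holds as a minor efficiency matter. The article commits to a two-category analysis of a five-category response, gives no reason of its own, and so gives up ordinal information on an outcome named in Objective 2. The loss of about 2 to 20 points rests entirely on the assumptions listed above. It would be near the top of that range only if answers are well spread and the program shifts them fairly evenly across the scale.

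**What to change.** In Humanistic endpoints, Data analysis, make the between-arm comparison of satisfaction at 9 months a proportional-odds (ordinal logistic) model of the 5-point response. Use study arm as the effect, with baseline score and study centre (the randomisation stratum) as covariates. Report the common odds ratio with its 95% CI for each WWCM arm against control and for in-person against web-based delivery. Keep the dichotomous percentage satisfied per arm beside it; that summary would also reveal a change confined to the cut.

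The cost is a short change of wording, with no new data and no more patients. The downsides are the proportional-odds assumption, which sparse low categories may strain, and an effect measure less intuitive than a percentage. Modelling the two items separately would give 2 × 3 = 6 comparisons, with no multiplicity adjustment planned, so the text should say which item, or which combination of the two, carries the comparison.
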